### Recruitment and randomization

The stroke survivors and their family caregivers will be selected during the hospital stay at SCU-Stroke. Those who meet the inclusion criteria and are eligible will be invited to participate in SHARE. Ethical procedures will be guaranteed and participants will be able to discontinue participation at any time in the research. Participants selected will receive a HV for baseline assessment within 7 days after discharge. Participants will be picked up, selected and evaluated by research assistants, who in order to minimize bias, will be responsible for: (1) obtaining the consent of family caregivers and the stroke survivors and (2) sending the participants baseline data for randomization.

The allocation of the participants in the IG or in the CG will be through simple randomization, through a numerical list generated by the website randomization.com. This list has a numerical order, in which each number is already assigned to one of the groups randomly. Thereafter, patients are given a number and their designation as they are included in the study. Randomization will occur after the baseline evaluation of stroke survivors and family caregivers, and will be performed by a trained research assistant who is not involved in the evaluation of the participants nor involved in the SHARE intervention.

The CG will receive conventional care, and the IG will receive the SHARE intervention. The assistant responsible for randomization will inform the interventional nurses which patients are assigned to the IG. The final evaluation of all participants will be performed by the same research assistants in the initial assessment 60 days after the date of the patient’s discharge from the hospital. The logistics of the study are presented in Fig. 2. Regarding the blindness, the trial will have outcomes obtained from blinded evaluators. Study participants will not be blind to the intervention.

**Fig. 2 Fig2:**
[figure not shown]
Logistic of the study

### Study treatment

#### Conventional care

The usual care consists of: (1) specialized care for stroke in the SCU-Stroke, carried out by a multiprofessional team (physicians, nurses, pharmacists, nutritionists, physiotherapists, speech therapists, social workers and psychologists), during hospitalization time and at the time of hospital discharge. This team will provide information about stroke survivors’ care and, in addition, will supply educational manuals containing various guidelines on illness, food/nutrition, medication care, mobility, bed placement, among others; (2) follow-up at the hospital outpatient clinic and (3) follow-up in primary health care services.

### Share

In addition to conventional care, SHARE participants will receive intervention that will: (1) guide the family caregiver to assist the stroke survivors in daily living at home and for the use of health services; (2) teach family caregivers about oral or nasoenteric feeding, personal hygiene, bathing, diaper changing, dressing and undressing, transfer, positioning, medication care, handling of devices, such as vesicles and ostomies, if necessary; (3) provide orientation related to the stroke, causes and consequences of the disease, how to prevent a new stroke, what resources the care network offers, and how to access them; (4) provide emotional support to the family caregiver and the stroke survivors and (5) provide educational material from the Health Education collection of Porto Alegre Clinical Hospital (HCPA) [29].

The intervention will be performed by a pair of nurses, trained to offer orientations based on an intervention protocol validated by consensus of specialists [30]. Three HVs will be performed within 1 month after hospital discharge (the first within 14 days, the second by 21 and the third within 30 days). Each intervention visit will last approximately 40 min.

The intervention will be offered verbally using the dialogical/problematizing educational approach developed by Freire in which the educator develops a dialogic process, stimulating the students’ reflective thinking capacity to transform their reality. In this approach an exchange of knowledge can occur in the socio-cultural context of the individual to be educated [31]. The interventionist nurses must: (1) consider the prior knowledge of family caregivers; (2) observe how they develop care according to their socio-cultural environment, experiences and financial resources; (3) encourage family caregivers to think reflectively about how care is being developed; (4) prepare the care intervention with the family caregiver using previous experiences along with the new information offered and (5) respect the knowledge of the family caregiver when performing the care.

### Data collection and outcomes

#### Primary and secondary outcomes

The primary outcomes will be: the caregiver’s burden and QofL, as measured by the Caregiver Burden Scale and by the World Health Organization Quality of Life–BREF (WHOQOL-BREF)_ and the World Health Organization Quality of Life (for caregivers aged over 60 years) (WHOQOL-OLD) [32–34]. Secondary outcomes: functional capacity measured by Functional Independence Measure (FIM) [35]; the hospital readmission of the stroke survivors and the use of health care services by participants after the stroke episode. Primary outcomes and functional capacity will be measured within 1 week after discharge and 2 months after discharge. The outcomes of hospital readmission and use of health services will be evaluated 60 days after discharge (Table 1).

**Table 1 Tab1:** Outcomes and time of data collection: stroke survivors and their family caregivers

Outcome and instrument	Family caregiver vs. stroke survivors	Data collection time	
		T0 (7 days)	T1 (60 days)
Primary outcomes			
Caregiver Burden Scale	Family caregiver	X	X
World Health Organization Quality of Life (WHOQOL-BREF and -OLD)	Family caregiver	X	X
Secondary outcomes			
Functional Independence Measure (FIM)	stroke survivor	X	X
Hospital readmission (yes/no)	stroke survivor		X
Use of health care services	Family caregiver and stroke survivor		X

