### WHOQOL-BREF

The instrument World Health Organization Quality of Life-BREF (WHOQOL-BREF) has been used to assess the QofL of the caregivers. This instrument, developed by the World Health Organization (WHO) in a cross-cultural perspective, has been used in national and international research with family caregivers of older adults people with stroke [37–40]. It consists in 26 questions and has two general questions about QofL. It has four domains: “Physical,” “Psychological,” “Social relations” and “Environmental” and there is no cut-off point for the worst or better QofL. The instrument provides a global score and for each of the four domains. The higher the score, the better the perception of QofL [41].

For caregivers aged older than 60 years, in addition to the WHOQOL-BREF, the WHOQOL-OLD module will be applied to evaluate the QofL of the older adults [42]. The OLD has six facets of four items each: “Sensory Abilities,” “Autonomy,” “Past, Present and Future Activities,” “Social Participation,” “Death and Dying” and “Intimacy.” The WHOQOL-BREF and the module OLD were validated for use in Brazil, presenting a Cronbach’s alpha of 0.91 and 0.885, respectively [33, 34].

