### Statistical methods

#### Sample size

The calculation of the sample was estimated by the burden outcome and was based on a study that demonstrated a difference between the caregiver’s burden and an improvement in their QofL after an educational intervention [5]. Considering a confidence level of 0.95, a statistical power of 0.80, a minimum effect size of 0.9 standard deviations between the groups regarding the burden and QofL, and a sample loss of 20%, the sample was calculated in 48 patients. There was a fair division between the two groups, with 24 patients in the IG and 24 patients in the CG. The statistical calculation was performed by the program WinPepi version 11.32 [45].

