### Data analysis

The analysis will be performed by intention-to-treat, where data from all participants (stroke survivors and their family caregivers) will be used regardless of the time they participated in the study [46]. Quantitative variables will be expressed as means and standard deviations or median and interquartile range. The Shapiro-Wilk test will be used to assess the distributions of the continuous outcomes. For the qualitative variables, absolute and relative frequencies will be presented. Student’s *t* test, the Mann-Whitney *U* test, Pearson’s chi-square test or Fisher’s exact test according to normality will be used to compare the groups. The linear regression model (quantitative outcomes) and the Poisson regression analysis (qualitative outcomes) will be applied, considering a *p* value of less than 0.20 in the bivariate analysis. A *p* < 0.05 will be considered. The Statistical Package for Social Sciences (SPSS) version 21.0 will be used for analysis.

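### Burden and quality of life are unranked primary outcomes at p < 0.05 with no success rule: if either suffices the error rate exceeds 5%, if both are required joint power is below 80%

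*Protocol article*

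**What the plan says.** Under Primary and secondary outcomes, the protocol article names as primary the caregiver's "burden and QofL, as measured by the Caregiver Burden Scale", followed by WHOQOL-BREF and a further instrument "for caregivers aged over 60 years) (WHOQOL-OLD". Table 1 places burden in one primary row and the two WHOQOL instruments together in another. Neither place ranks them.

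The WHOQOL-BREF section adds "The instrument provides a global score and for each of the four domains", and then "For caregivers aged older than 60 years, in addition to the WHOQOL-BREF, the WHOQOL-OLD module will be applied". For burden, the Caregiver Burden Scale section fixes a single total score, the mean of 22 items.

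The Data analysis section sets one threshold for all tests: "A *p* < 0.05 will be considered". It gives no order and no split of alpha.

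The Sample size section says that burden drove the calculation. It then states 80% power for "a minimum effect size of 0.9 standard deviations between the groups regarding the burden and QofL", with 20% loss and 24 per group.

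The first hypothesis expects the intervention group to do better on quality of life and also on burden. It is not written as a decision rule.

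**The concern.** Two primary constructs, measured with three instruments, share one unadjusted threshold, and the article does not say what counts as a positive trial.

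- If a significant result on either construct is enough, the trial has more than one chance of a false-positive claim, and the 5% level no longer describes the risk.
- If both must be significant, the error rate is safe, but a sample sized on one outcome does not give 80% power for the pair.

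The choice between these rules determines the trial's conclusion. Left open, it can be made after the results are seen.

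WHOQOL-OLD raises a separate problem. It carries a primary label but can be answered only by caregivers over 60, for whom no sample size was set.

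**Working it through.** **Inputs.** From the Sample size section: effect 0.9 SD, confidence level 0.95 (alpha 0.05, taken as two-sided), power 0.80, loss 20%, 24 per arm. The article gives neither the correlation between outcomes (range 0 to 0.9 used) nor the share of caregivers over 60 (20% to 40% assumed).

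**1. The plan's own figure.** n per arm = 2 × ((1.960 + 0.842) / 0.9)² = 19.38, rounded up to 20. Then 20 × 1.2 = 24 per arm, total 48. The stated size is reproduced for one outcome at two-sided 0.05. (Dividing by 0.8 instead gives 25 per arm, total 50.) After 20% loss, 24 × 0.8 = 19.2 remain, so 19 to 20 evaluable per arm is the relevant range.

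**2. Power for one outcome at 0.9 SD.** Normal approximation: Φ(0.9 × √(20/2) − 1.960) = Φ(2.846 − 1.960) = 0.81 with 20 per arm, and 0.80 with 19.2. On the t distribution: 0.79 with 20 and 0.77 with 19. The 80% is therefore about right for burden alone and for WHOQOL-BREF alone.

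**3. Either outcome suffices.** For independent tests, error = 1 − 0.95² = 9.75%. Simulation of correlated two-sided tests gives:

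| Correlation | Two tests | Three tests |
|---|---|---|
| 0 | 9.75% | 14.3% (1 − 0.95³) |
| 0.5 | 9.1% | 12.5% |
| 0.9 | 7.0% | 8.3% |

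The three-test column is illustrative. It assumes equal correlation in the same people, whereas WHOQOL-OLD is given to only some of them.

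**4. Both outcomes required.** The familywise error stays at or below 5%. Joint power, assuming a true effect of 0.9 SD on both:

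- Normal approximation, 20 per arm: 0.812² = 0.66 at correlation 0, 0.70 at 0.5, 0.76 at 0.9.
- t tests: 0.770² = 0.59 with 19 per arm and 0.792² = 0.63 with 20 per arm at correlation 0. Simulated two-sample t tests at correlation 0.9 give about 0.71 and 0.74.

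With independent outcomes, 80% joint power needs 26 evaluable per arm. That is a total of 64 when inflated the plan's way (26 × 1.2 = 31.2, so 32 per arm).

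**5. Alpha split over two outcomes (0.025 each).** Power per outcome is 0.73 (normal, 20 per arm) down to 0.67 (t, 19 per arm).

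**6. WHOQOL-OLD.** If 20% to 40% of 20 per arm are over 60, there are 4 to 8 per arm. Power at 0.9 SD is 0.19 to 0.39 on the t distribution (0.25 to 0.44 by normal approximation). The effect detectable with 80% power is 2.38 SD with 4 per arm and 1.51 SD with 8.

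**The case against.** The strongest defence has four parts.

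*The first hypothesis joins the outcomes, so both are required and error is not inflated.* This is fair as a reading. But the hypothesis is not a stated rule and the analysis section does not adopt it. If it is adopted, the joint power in step 4 applies.

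*The power statement is true.* This stands for each outcome singly, as step 2 shows. A reader might infer that the trial suffers error inflation and lost power at the same time, or that the 80% is simply wrong. Neither follows. Inflation belongs to an either-suffices rule and the joint power shortfall to a both-required rule. Without adjustment, the chance that at least one of the two is significant is 0.86 to 0.97 (20 per arm, normal approximation). The text needs only to say that the 80% is not joint.

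*The number of tests can be exaggerated.* This also stands. One could count burden plus four WHOQOL-BREF domains and reach 15% to 23%. But the article describes the domains as scores that the instrument yields and does not call each a primary outcome. Which score is analysed may be fixed in a fuller document. Nor is the over-60 group non-randomised: age is a baseline trait and allocation follows the baseline assessment. The weakness is the subset's size.

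*A separate analysis plan may hold a multiplicity rule.* It may. But the unranked primary labels and the single threshold are printed here, and no later rule gives a sample sized on one outcome 80% power for two or makes WHOQOL-OLD a powered primary.

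**Conclusion.** The point holds in conditional form. As printed, the plan allows two decision rules, and neither delivers both a 5% error rate and 80% power for the primary claim. If either of burden and WHOQOL-BREF suffices, familywise error is about 7% to 9.75%, or up to about 14% with WHOQOL-OLD as a third test. If both must succeed, error is controlled and joint power is about 0.66 to 0.76 (normal approximation, 20 per arm), or about 0.59 to 0.74 with t tests at 19 to 20 per arm. WHOQOL-OLD cannot support a primary conclusion under either rule.

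These figures assume two-sided tests, a 0.9 SD effect on each outcome, correlations of 0 to 0.9 and, for WHOQOL-OLD, that 20% to 40% of caregivers are over 60. The article gives neither the correlation nor the age share.

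**What to change.** Make these changes before outcomes are compared by group, and disclose them with their date:

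- Keep the Caregiver Burden Scale total score at day 60 as the first primary test, since it already drives the sample size.
- Name one WHOQOL-BREF score and test it at 5% only if burden is significant (fixed sequence). If both must remain equal primaries, use Holm.
- Report WHOQOL-OLD and the domain scores as descriptive secondary outcomes.
- In the Sample size section, state that the 80% power applies to burden alone, or to each outcome singly, and not to both jointly.

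No new participants are needed, but this is more than an edit. Recruitment began in May 2016 and was due to end in December 2017, before the article appeared in February 2018, so re-ranking a primary outcome this late needs a stated reason. Under the fixed sequence, quality of life loses its equal standing, and the chance of reaching a significant result on it is the joint power in step 4. Under Holm, both stay equal, but the power guaranteed per outcome falls to about 0.67 to 0.73.

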### Inclusion criteria

Participants will be included if they meet the following criteria: (1) to be a family caregiver of the aged (60 years old or more) stroke survivor with the first functional sequel from the SCU-Stroke; (2) stroke survivor with a minimum score of 2 on the Modified Rankin Scale (mRankin) at the time of discharge; (3) family caregiver 18 years or older; (4) a family caregiver who provides unpaid care and (5) stroke survivor who resides in the city of the study or another city within a distance of 20 km from the hospital.

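### WHOQOL-OLD sits among the primary outcomes but is given only to caregivers over 60, so the stated 80% power at 0.9 SD does not hold for it

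*Protocol article*

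**What the plan says.** All references are to the protocol article.

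- **Primary and secondary outcomes.** The primary outcomes are caregiver burden and caregiver quality of life. Quality of life is measured by WHOQOL-BREF and by the "World Health Organization Quality of Life (for caregivers aged over 60 years) (WHOQOL-OLD"). Table 1 puts both instruments in one row under the primary outcomes, for the family caregiver, and does not repeat the age limit.
- **WHOQOL-BREF (Instruments).** "For caregivers aged older than 60 years, in addition to the WHOQOL-BREF, the WHOQOL-OLD module will be applied". WHOQOL-BREF itself carries no age limit.
- **Inclusion criteria.** The 60-year threshold applies to the stroke survivor. The caregiver criterion is "family caregiver 18 years or older".
- **Recruitment and randomization.** Allocation is by simple randomization. Stratification by caregiver age is not mentioned.
- **Sample size.** The calculation is based on burden. It uses a 0.95 confidence level, "a statistical power of 0.80", "a minimum effect size of 0.9 standard deviations between the groups regarding the burden and QofL", and 20% loss, and arrives at 48, 24 per group. WHOQOL-OLD is not named there, and no expected number of caregivers over 60 is given.

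**The concern.** The article fixes three things that do not fit together: which measures are primary, who completes them, and what power the sample gives for quality of life. A reader who takes the outcome list and the Sample size section together will apply 80% power at 0.9 SD to every primary measure. For WHOQOL-OLD the number analysed will be whatever part of the sample happens to be over 60.

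Two consequences follow. A non-significant WHOQOL-OLD result could be read as failure on a primary outcome when the comparison had much less than the stated power. A significant one might rest on few caregivers. In either case it would describe only older caregivers, whereas the first research objective concerns family caregivers of stroke survivors in general.

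This is separate from multiplicity. Tested alone at 5%, WHOQOL-OLD would still have fewer participants than the power statement assumes.

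**Working it through.** **Inputs from the Sample size section.** Alpha 0.05 ("Considering a confidence level of 0.95"; sidedness is not stated), power 0.80, difference 0.9 SD, loss 20%, equal groups, total 48.

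**Step 1: reproduce the 48.** With the normal approximation, two-sided:

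n per arm = 2 × (1.960 + 0.842)² / 0.9² = 2 × 7.85 / 0.81 = 19.4, rounded up to 20, so 40 evaluable.

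Adding 20% gives 40 × 1.20 = 48, the stated total. (Dividing by 0.80 would give 50.) A one-sided test would need only 16 per arm and does not reproduce 48, so two-sided is assumed from here on.

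**Step 2: slack in the full sample.** With all 40 evaluable caregivers (20 per arm), power at 0.9 SD is 81% by the normal approximation and 79% by the t test. There is almost no reserve, so an outcome observed in clearly fewer than all evaluable caregivers falls below 80%.

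**Step 3: power in the over-60 subset.** The share over 60 is not in the document, so it is an assumption, shown over a range. With share f, n per arm = 40f / 2 = 20f if the arms are equal. Power comes from the two-sided 5% t test with 2n − 2 degrees of freedom and non-centrality 0.9 × √(n/2).

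| Assumed share over 60 | n per arm | Power at 0.9 SD | Difference for 80% power |
|---|---|---|---|
| 25% | 5 | 24% | 2.02 SD |
| 30% | 6 | 29% | 1.80 SD |
| 50% | 10 | 48% | 1.32 SD |
| 75% | 15 | 66% | 1.06 SD |
| 100% | 20 | 79% | 0.91 SD |

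**Step 4: most favourable case, no loss at all.** If all 48 stay, 80% power needs 40 caregivers over 60 by the normal approximation (40/48 = 83%) or 42 by the t test at 21 per arm (42/48 = 88%).

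**Step 5: unequal arms.** The table assumes equal arms, which is the best case. Suppose 10 evaluable caregivers are over 60. A 5/5 split gives 24% power and a 3/7 split gives 21%. If each is assigned independently with probability one half, a split of 3/7 or worse has probability 2 × (1 + 10 + 45 + 120) / 1024 = 34%. The further loss is modest; the size of the subset matters far more.

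**The case against.** The strongest reply is that WHOQOL-OLD was never meant to stand alone. The outcome section names two constructs, burden and quality of life, and then their instruments. Table 1 gives the two WHOQOL instruments a single row, and the Instruments section describes WHOQOL-OLD as a module added to WHOQOL-BREF. The sample was sized on burden, and the Sample size section does not name WHOQOL-OLD, so WHOQOL-BREF can satisfy its reference to quality of life. How two scores are ranked or combined is often left to an analysis plan, which is not shown.

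Much of this stands. No planning figure specific to WHOQOL-OLD exists to be contradicted, and burden and WHOQOL-BREF keep their planned numbers, so the quality-of-life objective as a whole is not left without power. It does not settle the matter, because the article itself places WHOQOL-OLD under the primary outcomes and nowhere gives WHOQOL-BREF priority.

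A reader might go further and infer that the trial cannot detect 0.9 SD on WHOQOL-OLD, or that a null result there is likely even if the intervention works as planned. The document does not support either. The share over 60 is unknown and nothing caps it at one half. At 75% the power is about 66%, so a true 0.9 SD effect would more often than not be detected. What can be said is that the stated 80% is not secured.

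**Conclusion.** The point holds in a limited form. WHOQOL-OLD has primary status, an age-restricted population that the design does not secure, and a sample-size statement whose power does not carry over to it. At assumed shares of 25% to 75% over 60, power at 0.9 SD is about 24% to 66% instead of 80%. Even with no loss, more than four in five caregivers would have to be over 60 to reach 80%.

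These figures assume a two-sided 5% t test and equal subset arms. Those in the table also assume 40 evaluable caregivers and the same 20% loss in older caregivers as in all. The share over 60 is the unknown that matters most. The power stated for burden and WHOQOL-BREF is unaffected.

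**What to change.** 1. In the outcome section and Table 1, name WHOQOL-BREF as the measure that carries the primary quality-of-life conclusion.
2. In the same places, make WHOQOL-OLD a secondary or exploratory outcome in caregivers over 60, reported with the number analysed per group and the estimated difference with its confidence interval.
3. In the Sample size section, state that the 0.9 SD and 80% power figure does not apply to WHOQOL-OLD.

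Data collection does not change. The cost is more than wording, however. The Trial status section shows recruitment under way since May 2016, with completion due in December 2017, so taking a listed measure out of the primary set changes the outcome hierarchy late. It should be a dated, justified amendment made before outcome data are examined by group; otherwise it may look like outcome switching. The trial also gives up a confirmatory claim on WHOQOL-OLD, which the design does not secure in any case.
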